## CHILDREN

At baseline and 6 months, children's height, weight and waist circumference will be measured at preschools. In addition, (some) children will wear an accelerometer for 7 consecutive days. Height (cm) will be measured to the nearest 0.1 cm in standing position using a portable stadiometer (Seca 213). Weight (kg) will be measured to the nearest 0.1 kg in standing position without shoes or heavy clothing using a portable weighing scale (Seca 813). BMI ( $\text{kg/m}^2$ ) will be calculated and BMI z-scores will be assessed using World Health Organisation reference data (WHO Anthro). Waist circumference (cm) will be measured to the nearest 0.1 cm in standing position (at the mid-point between the lower costal margin and the level of the anterior superior iliac) with a standard tape measure (28). All procedures will be performed using Standard Operating Procedures by trained research staff/students of the AUAS. Physical activity will be assessed using a 3-axis accelerometer: ActiGraph GT3X+ (29). The accelerometers will be placed on the right hip using an elastic belt. Children will wear the accelerometers for 7 consecutive days during waking hours, excluding activities including water such as bathing/showering and swimming. Data will be derived using a 10-s epoch. Counts per minute based on vector magnitude will be extracted. In times

of corona, physical measurements at preschools will not be performed as parents and researchers are not allowed to enter the preschools. When it is allowed again to enter preschools, the researchers will start performing the measurements and collect data on children's weight development and physical activity levels.

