### 4.2 Inclusion criteria

- Urban preschools must provide play-based education to be eligible to be included in this study.
- ECEC teachers and parents must provide written Informed Consent for participation.
- Parents must provide additional written Informed Consent for the participation of their child.
- Parents must have a child at the participating urban preschools and the child must be between 2 to 3.5 years old to be eligible to participate in this study.

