### 4.4 Sample size calculation

It is aimed to include 160 ECEC teachers ( $n = 80$  in the intervention group and  $n = 80$  in the control group). This sample size is based on a medium effect size (Cohen's  $d: 0.50$ ), a 2-sided alpha of 5%, a power of 80%, a design effect (mean cluster size: 3, ICC: 0.05) and a 15% drop-out rate. Furthermore, it is aimed to include 320 parents and 320 children ( $n = 160$  parents and their 160 children in the intervention group and  $n = 160$  parents and their 160 children in the control group). Considering a 2-sided alpha of 5% and a power of 80%, it is possible to obtain, with 160 parents and children per group, a small to medium effect size (Cohen's  $d: 0.35$ ) (mean cluster size: 6, ICC: 0.02, 15% drop-out rate).

Egert et al. (2020), conducted a meta-analysis and showed a small to medium effect of professional development in ECEC on the quality of teacher-child interactions (16).

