**Height (cm)**

*Measurement at baseline and at 6 months.*

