### **8.2 Secondary study parameter(s)**

Linear mixed model analyses will be performed to determine the effects of the preschool-based intervention on the secondary outcome measures. Childcare organisation and preschool location will be added as random intercepts to take into account the clustered

data structure. Overall models with treatment (intervention or control group) and the baseline value of a specific outcome measure will be made to assess the overall treatment effect of the intervention. In addition, the models will be adjusted for age, ethnicity and level of education.

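### Models for child height, weight and waist in cm and kg take no account of the actual measurement interval or the child's sex, which costs precision and leaves any one-arm timing lag uncorrected

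*Protocol*

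**What the plan says.** Section 2 lists children's height, weight, waist circumference and BMI z-score as separate secondary objectives. Section 6.1.2 gives height in cm, weight in kg and waist in cm. The timing given for height is "Measurement at baseline and at 6 months", and weight and waist have the same schedule. Only BMI is put on an age- and sex-specific scale: "BMI z-scores will be assessed using World Health Organisation reference data (WHO Anthro" (6.3, Children).

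Section 8.2 models every secondary outcome with treatment and its baseline value, with random intercepts for childcare organisation and preschool. It continues: "In addition, the models will be adjusted for age, ethnicity and level of education". Children's sex is collected (6.1.3) but is not in that list. Section 8.1 names the teacher's age for the primary model. Section 8.2 covers teacher, parent and child outcomes and does not say whose age is meant.

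On timing, "the child must be between 2 to 3.5 years old to be eligible to participate in this study" (4.2). Section 3 places data collection at baseline and 6 months without a window. The Summary counts the six months for the main questionnaire outcome from when the intervention begins. Section 5.1 gives control preschools no training or Toolkit. Section 6.3 has children measured at the preschools, and not while access is barred because of corona.

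**The concern.** Children of this age grow quickly, so a measurement taken a few weeks late differs in cm and kg for that reason alone. A BMI z-score calculated at the exact age takes this into account. A raw height, weight or waist does not, unless the model contains the interval.

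Visits are organised by preschool, which is also the unit of randomisation, so variation in timing would fall largely between clusters. There it directly widens the standard error of the treatment effect. If timing also differed systematically between arms, the difference would appear as a treatment effect. The Summary's anchor makes this possible: if child visits followed the same clock, any delay between baseline and training would lengthen the interval in the intervention arm only.

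**Working it through.** **The plan's own figure.** Section 4.4 states that, "with 160 parents and children per group, a small to medium effect size" (Cohen's d 0.35) can be detected, with "mean cluster size: 6, ICC: 0.02, 15% drop-out rate", two-sided alpha 5% and power 80%.
- n per arm = 2 × (1.960 + 0.842)² / 0.35² = 128.1, rounded up to 129.
- Design effect = 1 + (6 − 1) × 0.02 = 1.10.
- Effective n = 160 × 0.85 / 1.10 = 123.6. Detectable d = 2.802 × √(2 / 123.6) = 0.356; power at d = 0.35 is 78.6%.

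The figure is reproduced closely and is not in dispute. It gives the number of clusters: 160 / 6 ≈ 27 preschools per arm, with about 6 × 0.85 ≈ 5 children each at follow-up. The 0.35 cm used below is an illustrative height effect and is unrelated to the d of 0.35.

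**Equal intervals.** Simulation on assumed growth: height 87 cm at age 2, velocity about 9 cm a year and falling, between-child SD 3.2-4 cm, 54 preschools × 5 children, cluster-robust errors, 1,500 runs.

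| Model | No effect: mean estimate | No effect: rejection | True 0.35 cm: power |
|---|---|---|---|
| Raw + baseline | 0.00 cm | 6.3% | 90% |
| Raw + baseline + age | 0.00 cm | 6.5% | 92% |
| z-score + baseline | 0.00 SD | 5.9% | 93% |

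An imposed age imbalance of 0.1 year gave a bias of −0.05 cm with baseline only and 0.00 cm once age was added. The raw scale does no material harm here. The standard error of the raw + baseline + age model was 0.101 cm.

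**Intervals that vary by preschool.** Take 8 cm a year at mid-range age, which is 8 / 52.18 = 0.153 cm per week.
- Timing scatter in height = SD in weeks × 0.153. For 2 weeks it is 0.307 cm; for 3 weeks, 0.460 cm.
- Added standard error = scatter × √(2 / 27). For 2 weeks it is 0.084 cm; for 3 weeks, 0.125 cm.
- Total standard error = √(0.101² + 0.084²) = 0.131 cm, or √(0.101² + 0.125²) = 0.161 cm.
- Power = Φ(0.35 / SE − 1.96): 0.93 with no variation, 0.76 at 2 weeks, 0.59 at 3 weeks.

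This agrees with direct simulation of varying intervals: about 92%, 77% and 57%. z-scores at exact age, or an interval covariate, kept power at 92-94%. A second simulation with other assumptions (46 preschools × 6 children, residual SD 0.8 cm) gave 85%, 64% and 47% for the raw model, against 86%, 83% and 84% for z-scores.

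**A lag in one arm.** Each week adds about 0.15 cm at 8 cm a year (9 / 52.18 = 0.17 cm at 9 cm a year). In the second simulation, with no true effect, an interval SD of 2 weeks and the intervention arm seen later:

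| Mean lag | Raw + baseline + age: false positives | z-score: false positives |
|---|---|---|
| About 1 week | 19% | 5% |
| About 2 weeks | 59% (spurious 0.32 cm) | 4% |
| 1 month | 99% (spurious 0.64 cm) | 5% |

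Adding the child's age and sex to the raw model did not remove this; using the age at each measurement did.

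**Weight.** Assuming a gain of 0.8-1.3 kg in 6 months (26.09 weeks), each week of lag is worth 0.8 / 26.09 = 0.03 kg to 1.3 / 26.09 = 0.05 kg.

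**The case against.** A reader might infer that normal growth by itself can mimic an effect, or that outcomes in cm and kg are invalid in this age group. The documents do not support either reading. Effects are contrasts with a concurrent control group, randomised by preschool in size-matched pairs (6.2) and scheduled for the same two timepoints (Section 3). Growth over equal intervals cancels, every model contains the baseline value, and the adjusted models add age. Chance imbalance in age or sex is then a minor matter. This part of the objection stands in full.

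It can also be said that nothing shows intervals differing by arm, and that chance would not produce a large difference. With an SD of 3 weeks (0.69 month) at preschool level, the standard error of the difference in mean interval is 0.69 × √(2 / 27) = 0.19 month, so a one-month gap would be more than 5 standard errors out. That is right about chance, but it does not cover a systematic lag. At an assumed 0.5-0.83 cm a month, the same 0.19 month is 0.09-0.16 cm, as large as the 0.101 cm standard error that exists without timing variation. That is the loss of precision. The preschool random intercept keeps the error bars honest but does not recover it.

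Finally, covariates could be left to the statistical analysis plan, which is not shown and may deal with some of this. But the protocol itself fixes the outcome scale and the adjustment set, and standardises one body measure of four.

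**Conclusion.** The point holds as one about measurement timing and is a modest, inexpensive improvement to secondary outcomes. With equal intervals the planned contrast is unbiased and about as powerful as a z-score analysis. With intervals varying between preschools by an SD of 2-3 weeks, power for a 0.35 cm height effect falls from about 92% to about 77-57%. A systematic lag in one arm would add about 0.15 cm of height per week.

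The growth rates, residual variation and interval SDs are assumptions; the protocol gives none of them. A lag is a possibility opened by the wording and is not shown to be planned: the intervention-start anchor is stated for the questionnaire, and the child measurements are listed only as baseline and 6 months. Leaving out sex and not saying whose age is meant are small matters of precision and clarity.

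**What to change.** In 6.3 and 8.2, for child body measurements:
- Analyse height and weight as age- and sex-standardised z-scores at the exact age at each measurement, or keep cm and kg and adjust for the child's sex, exact age at baseline and actual interval.
- Use the second option for waist.
- Report raw values alongside.
- State that age in child models is the child's age.
- Time follow-up from the baseline measurement in both arms.

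If intervals turn out to differ by arm with little spread within arms, an interval covariate cannot be separated from treatment. z-scores do not have that weakness, which favours them for height and weight.

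The cost is a few sentences and keeping the date of each measurement. The planned BMI z-scores already need the child's age and sex. The protocol cites the WHO reference data for BMI only, so their use for height and weight should be confirmed; the covariate option does not depend on it. The drawback is that z-scores are slightly less intuitive than cm or kg, which reporting the raw values offsets.

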#### **6.4 Withdrawal of individual subjects**

Participants can leave the study at any time for any reason if they wish to do so without any consequences. Parents can end the child's participation at any time for any reason if they wish to do so without any consequences. If a child expresses an objection in the measurements, the measurements will be discontinued.

#### **6.5 Replacement of individual subjects after withdrawal**

Participants will not be replaced after withdrawal.

#### **6.6 Follow-up of subjects withdrawn from treatment**

There will be no follow-up of patients who withdraw from the study.

#### **6.7 Premature termination of the study**

There are no reasons available for discontinuation of this study.

## 7. SAFETY REPORTING

### 7.1 Temporary halt for reasons of subject safety

In accordance to section 10, subsection 4, of the WMO, the sponsor will suspend the study if there is sufficient ground that continuation of the study will jeopardise subject health or safety. The sponsor will notify the accredited METC without undue delay of a temporary halt including the reason for such an action. The study will be suspended pending a further positive decision by the accredited METC. The investigator will take care that all subjects are kept informed.

### 7.2 AEs and SAEs

#### 7.2.1 Adverse events (AEs)

Adverse events are defined as any undesirable experience occurring to a subject during the study, whether or not considered related to the experimental intervention. All adverse events reported spontaneously by the subject or observed by the investigator or his staff will be recorded.

#### 7.2.2 Serious adverse events (SAEs)

A serious adverse event is any untoward medical occurrence or effect that:

- results in death;
- is life threatening (at the time of the event);
- requires hospitalisation or prolongation of existing inpatients' hospitalisation;
- results in persistent or significant disability or incapacity;
- is a congenital anomaly or birth defect; or
- any other important medical event that did not result in any of the outcomes listed above due to medical or surgical intervention but could have been based upon appropriate judgement by the investigator.

An elective hospital admission will not be considered as a serious adverse event.

The investigator will report all SAEs to the sponsor without undue delay after obtaining knowledge of the events, except for the following SAE:

- an elective hospital admission.

The sponsor will report the SAEs through the web portal *ToetsingOnline* to the accredited METC that approved the protocol, within 7 days of first knowledge for SAEs that result in death or are life threatening followed by a period of maximum of 8 days to complete the initial preliminary report. All other SAEs will be reported within a period of maximum 15 days after the sponsor has first knowledge of the serious adverse events.

### **7.3 Follow-up of adverse events**

All AEs will be followed until they have abated, or until a stable situation has been reached. Depending on the event, follow up may require additional tests or medical procedures as indicated, and/or referral to the general physician or a medical specialist.

SAEs need to be reported till end of study within the Netherlands, as defined in the protocol.

## **8. STATISTICAL ANALYSIS**

Descriptive statistics (n (%)) or mean  $\pm$  standard deviation) will be used to describe the characteristics of the study population.

Linear mixed model analyses will be performed to determine the effects of the preschool-based intervention on the primary and secondary outcome measures. Childcare organisation and preschool location will be added as random intercepts to take into account the clustered data structure. Overall models with treatment (intervention or control group) and the baseline value of a specific outcome measure will be made to assess the overall treatment effect of the intervention. In addition, the models will be adjusted for age, ethnicity and level of education.

Regression coefficients ( $\beta$ ), P values and 95% confidence intervals (CI) will be computed for all crude and adjusted mixed models. The statistical significance will be at  $p < 0.05$ .

A Statistical Analyses Plan including details of statistical analyses will be finalised before dataset closure.

### **8.1 Primary study parameter(s)**

Linear mixed model analyses will be performed to determine the effects of the preschool-based intervention on the primary outcome measure. Childcare organisation and preschool location will be added as random intercepts to take into account the clustered data structure. Overall models with treatment (intervention or control group) and the baseline value of a specific outcome measure will be made to assess the overall treatment effect of the intervention. In addition, the model will be adjusted for ECEC teachers' age, ethnicity and level of education.

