## 6.2 Randomisation, blinding and treatment allocation

Randomisation will be performed before the start of the study on the level of preschools within participating childcare organisations. The randomisation will be performed by an independent researcher of the AUAS with the use of computer-generated randomisation lists. It concerns a stratified randomisation by childcare organisation to achieve balance in the number of preschools within each organisation that will receive the intervention or not. As preschools within each organisation differ in location size (and therefore the number of eligible participants), we will 1) order preschools by location size, 2 ) match preschools in pairs based on location size and 3) randomly allocate 1 preschool to the intervention group and the other to the control group. 1 member of the research staff ([name]) will be blinded for allocation and perform final analyses. ECEC teachers, parents and other members of the research staff will not be blinded as the intervention does not allow for this.

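### Preschools are randomised within organisation in pairs matched on location size, but the models omit size and enter three organisations as a random intercept (minor)

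*Protocol*

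**What the plan says.** **Randomisation (Protocol 6.2).** "It concerns a stratified randomisation by childcare organisation to achieve balance" in the number of preschools per arm. Because preschools differ in size, and so in how many people can take part, the protocol orders them by size, will "match preschools in pairs based on location size", and randomises one of each pair to the intervention.

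**Organisations (Protocol 4.1).** Three childcare organisations are named.

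**Analysis (Protocol 8, 8.1 and 8.2).** The same linear mixed model is written out three times: "Childcare organisation and preschool location will be added as random intercepts to take into account the clustered data structure". The fixed part is treatment and the baseline value of the outcome. The adjusted versions add age, ethnicity and level of education. In these sentences the preschool location is the cluster itself, not its size. Section 8 leaves further details to a statistical analysis plan, to be finalised before dataset closure.

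**Sample size (Protocol 4.4).** "It is aimed to include 160 ECEC teachers", with "a 2-sided alpha of 5%, a power of 80%, a design effect (mean cluster size: 3, ICC: 0.05) and a 15% drop-out rate" and Cohen's d of 0.50. For the others, "it is aimed to include 320 parents and 320 children", with d of 0.35 and "mean cluster size: 6, ICC: 0.02, 15% drop-out rate".

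**The concern.** An analysis should normally contain the factors that constrained the allocation. Here location size did so, and no stated model contains it. If size is related to partnership scores, matching has already balanced that variation between the arms, but the model counts it as random preschool variation when it computes the standard error of the treatment effect. The reported uncertainty is then larger than the design warrants.

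Organisation is in the model, but as a random intercept. A variance estimated from three levels is poorly determined and may be set to zero or fail to settle. A fixed effect is the usual choice for a stratification factor with so few levels.

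At stake are a little precision and a model that fits cleanly. The validity of the test is not at stake.

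**Working it through.** **1. The plan's own figures.**
- Teachers: n per arm = 2(1.960 + 0.842)² / 0.50² = 62.8, so 63. Design effect 1 + (3 − 1)(0.05) = 1.10 gives 69.3. Allowing for 15% loss gives 80 (× 1.15) or 82 (÷ 0.85). The stated 80 per arm is reproduced.
- Parents: 2(1.960 + 0.842)² / 0.35² = 128.1, so 129. Design effect 1 + (6 − 1)(0.02) = 1.10 gives 141.9, then 164 (× 1.15) or 167 (÷ 0.85), against 160 stated. With 160 per arm the detectable d is 0.352 to 0.356, which agrees with the stated 0.35.

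Neither calculation contains a term for matching or stratification.

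**2. Assumptions for the check.** The number of preschools is not stated; 160/3 = 320/6 = 53.3, so 54 is used (27 per arm). Analysed cluster sizes after 15% loss are 3 × 0.85 = 2.55 teachers and 6 × 0.85 = 5.1 parents. Let f be the share of between-preschool variance explained by size. The documents do not give f, so it runs from 0 to 1. Equal cluster sizes are assumed, and no gain from the baseline value is modelled.

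**3. Overstatement of the standard error.** The variance of a preschool mean, in SD units, is V = ICC + (1 − ICC)/m. With size accounted for it is V_f = (1 − f)·ICC + (1 − ICC)/m. The overstatement is √(V/V_f).
- Teachers, f = 0.5: V = 0.05 + 0.95/2.55 = 0.4225; V_f = 0.3975; ratio 1.031. The actual error rate at nominal 5% is 2[1 − Φ(1.96 × 1.031)] = 4.3%.
- Parents, f = 0.5: V = 0.02 + 0.98/5.1 = 0.2122; V_f = 0.2022; ratio 1.024; error rate 4.5%.
- Ceiling (f = 1): the variance falls by 0.05/0.4225 = 11.8% for teachers and 0.02/0.2122 = 9.4% for parents. In simulation (20,000 replicates per setting) the planned type of model then had an error rate of 3.9% to 4.0%.

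**4. Power under three analyses.** The planned model has 52 degrees of freedom on preschool means, the size covariate leaves 51, and a pair-level analysis leaves 26.

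| | f | Planned | Size covariate | Pair-level |
|---|---|---|---|---|
| Teachers, d 0.50 | 0 | 79.4% | 79.2% | 77.7% |
| | 0.25 | 79.7% | 80.4% | 78.9% |
| | 0.5 | 80.1% | 81.6% | 80.1% |
| | 1 | 80.9% | 84.0% | 82.6% |
| Parents, d 0.35 | 0 | 78.4% | 78.2% | 76.7% |
| | 0.25 | 78.7% | 79.2% | 77.6% |
| | 0.5 | 78.9% | 80.1% | 78.6% |
| | 1 | 79.5% | 82.1% | 80.6% |

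The planned column uses a normal approximation, the other two the non-central t. With the non-central t throughout, teacher power at f = 0 is 79.2% on 52 degrees of freedom, 79.2% on 51 and 79.1% on 49 (size plus two for organisation). So 0.2 points is an upper figure for the cost.

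**5. Organisation: random, fixed or omitted** (simulation, teachers, f = 0.25, organisation variance 0.02).

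| Organisation | Power | Mean interval width | Type I error |
|---|---|---|---|
| Random | 80.1% | 0.703 | 4.9% |
| Fixed | 79.8% | 0.707 | 4.7% |
| Omitted | 78.6% | 0.718 | 4.6% |

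With no organisation variance and f = 0, the figures are 79.8% (random) and 79.3% (fixed). Random coding therefore loses no precision and is marginally the narrower.

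**The case against.** Much of the opposing case stands.

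- **Purpose of the pairing.** Section 6.2 explains it by the number of eligible participants, that is, by balancing numbers between the arms. Nothing in the protocol says that size predicts partnership scores. The half share is therefore only an assumption, and the true loss could be nil.
- **Baseline value.** It is in every model and would absorb part of any stable difference linked to size. The figures above take no account of this.
- **Statistical analysis plan.** Details are left to a document that is not shown and that could add these terms. This softens the point but does not remove it, because the protocol states the random part and the covariates explicitly, three times.

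A reader might also infer more than the documents support:

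- **That the power is undercut.** It is not. Section 4.4 takes no credit for matching.
- **That random organisation wastes precision, or does nothing.** Neither holds. Random and fixed coding give almost the same interval, and omitting organisation is worse than either.
- **That the model must contain the pairs.** A pair-level analysis lowers teacher power from 79.4% to 77.7% if the pairs explain nothing and only breaks even when they explain half. A rule to drop a pair intercept whose variance is estimated at zero would also make the model depend on the data.
- **That standard errors are 6% to 10% too large.** For parents this needs an ICC of 0.05 (ratio 1.058) or 0.10 (1.105), against the stated 0.02.

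**Conclusion.** The mismatch is real and stands in fixed text: location size constrained the allocation and is in no stated model, and a three-level stratification factor is coded as random. The consequence is small. At the stated ICCs, and if size explains half of the between-preschool variance, standard errors are about 2% to 3% too large and the error rate is 4.3% to 4.5% instead of 5%. Even if size explains everything, the test is only conservative. Adding size changes power by −0.2 to about +3 points for teachers and −0.2 to +2.6 for parents. The criticism of the organisation term concerns stability and clean fitting; no harm to the treatment estimate was found. These figures rest on about 54 preschools of equal size and on an assumed range for f. Severity: minor.

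**What to change.** In the overall and adjusted models of Protocol sections 8, 8.1 and 8.2, enter childcare organisation as a fixed effect (three categories, 2 degrees of freedom) and location size as a fixed covariate (1 degree of freedom), using the size measure by which preschools were ordered for randomisation. Keep preschool as a random intercept. A random intercept for the matched pair belongs at most in a prespecified sensitivity analysis.

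The change is one of wording and needs no new data, since size is already known. It can be made in the protocol or in the statistical analysis plan before dataset closure, with the two texts brought into line. If size turns out to be unrelated to the outcome, the covariate costs at most about 0.2 power points. Fixed instead of random coding of organisation cost 0.3 to 0.5 points in the teacher settings quoted above, which is the price of not relying on a variance estimated from three levels.
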